## Abstract

**Background:**

Insomnia is a common sleep-related condition that includes dissatisfaction with sleep quality, difficulty in initiating or maintaining sleep, and early morning waking. Insomnia can affect daytime functioning by causing fatigue, depression, and anxiety. Medications are the most common method for the management of insomnia but can cause adverse effects, including psychological and physical dependence, residual daytime sedation, and cognitive impairment. Acupuncture is a common traditional Chinese therapy. It has been used in the treatment of insomnia, depression, and anxiety in China. However, there are no high-quality studies focusing on acupuncture for insomnia, especially for depression and anxiety due to insomnia. Therefore, we have designed a randomized controlled trial (RCT) involving a placebo control to ensure blinding of participants to investigate the effects of acupuncture on insomnia in improving sleep quality and psychosocial symptoms.

**Methods:**

We have designed a single-center, parallel-group, single-blinded RCT. A total of 252 participants who meet the eligibility criteria will be randomly allocated into a manual acupuncture group or sham acupuncture group in a 1:1 ratio. All participants will receive 24 sessions of acupuncture (30 min per session, three sessions per week for 8 weeks). Participants will be assessed using the Pittsburgh Sleep Quality Index score, self-assessment anxiety scale, self-assessment depression scale, and Medical Outcomes Study 36-Item Short-Form Health Survey at baseline and 8 weeks. All analyses will be based on an intention-to-treat principle. The results will be published in an international peer-reviewed journal.

**Discussion:**

The results of this study are expected to clarify the effects of acupuncture on sleep quality and psychosocial symptoms in patients with insomnia. This will contribute to the clinical practice of acupuncture in the management of insomnia.

**Trial registration:**

Chinese Clinical Trail Registry ChiCTR2100049172. Registered on 24 July 2021.

## Background

As a major public health problem, insomnia is defined as sleep difficulties including dissatisfaction with sleep quality, difficulty in initiating or maintaining sleep, and early morning waking, which can affect daytime functioning, and cause fatigue, depression, anxiety, and other symptoms [1, 2]. The prevalence of insomnia is 10–20%, and about 50% of cases involve chronic insomnia, which is defined as suffering from this condition for at least 3 nights each week for 1 month or more [3]. In China, the prevalence of insomnia is approximately 15% [4]. Sleep disturbance is thought to be closely associated with psychological disorders, including depression and anxiety [5]. A survey reported that nearly 30% of the population suffers from psychological disorders due to busy lives and high-pressure jobs, and most affected individuals experience different degrees of insomnia. However, insomnia has not yet been effectively resolved [6, 7].

Medications, such as antidepressants and melatonin, are the most commonly used treatments in the management of insomnia [8]. The use of sleeping pills is common among adults, and middle-aged women with higher education are more likely to have used anti-insomnia drugs [9]. However, adverse effects, including psychological and physical dependence, residual daytime sedation, and cognitive impairment, should not be ignored [10]. Therefore, the American Academy of Sleep Medicine and the American College of Physicians recommend non-pharmacological therapies, including acupuncture and relaxation, first-line treatment options for insomnia [11, 12].

Acupuncture is popular and safe traditional Chinese therapy. It has been used in the treatment of insomnia, depression, and anxiety in China for thousands of years. Acupuncture may restore physiological function through the insertion of needles to stimulate acupoints. Studies have indicated that acupuncture could be effective for sleep disorders by increasing the content of serotonin and aminobutyric acid [13], reducing glutamate levels [14], and improving the function of central inhibition [15]. With better sleep quality, depression and anxiety in patients with insomnia are improved. Previous reviews have shown that acupuncture affects insomnia, but there are no high-quality studies focusing on acupuncture for insomnia, especially for treating depression and anxiety due to insomnia [16, 17].

Therefore, it is important to conduct high-quality randomized controlled trial (RCT) to assess the effects of acupuncture on sleep quality, depression, and anxiety in patients with insomnia, with sham acupuncture as control. In this study, we designed a randomized, parallel-group, single-blinded trial to investigate the effects of acupuncture for insomnia in improving sleep quality and psychosocial disorders.

## Methods/design

### Study design

A single-center, parallel-group, single-blinded randomized controlled superiority trial has been designed to compare the effects of manual acupuncture and sham acupuncture in the treatment of insomnia. All participants will receive manual acupuncture or sham acupuncture during three sessions per week over 8 weeks. The study has been approved by the ethics committee of the Shaanxi Provincial Hospital of Chinese Medicine (2020-17). The study protocol follows the Standard Protocol Item Recommendations for Interventional Trials (SPIRIT) guidelines and Standards for Reporting Interventions in Controlled Trials of Acupuncture (STRICTA). This study protocol is funded by the Chinese Clinical Trials Registry. The registry number is ChiCTR2100049172, and the registration date is July 24, 2021. The study procedure is illustrated in Fig. 1. The trial schedule is listed in Table 1.

**Fig. 1 Fig1:**
[figure not shown]
The study procedure

**Table 1 Tab1:** The trial schedule

Items	Before enrollment (week − 1)	Intervention period (weeks 1–8)	End of intervention (week − 9)
Inclusion criteria	√		
Exclusion criteria	√		
Informed consent	√		
Baseline measurement	√		
Randomization and allocation	√		
PSQI	√		√
Quality of life	√		√
Depression	√		√
Anxiety	√		√
Blinding success rate			√
Adverse events			√

*PSQI* Pittsburgh Sleep Quality Index

### Participants

### Recruitment

Participants will be recruited from among outpatients of the Shaanxi Provincial Hospital of Chinese Medicine by advertisements on community boards and online social media (WeChat). Patients, who are interested in this study, will be asked to communicate with the researchers face-to-face for more detailed information including interventions, assessments, benefits gained from this trial, and potential adverse reactions. Before randomization, written informed consent will be obtained from all participants prior to their participation. Detailed attention, including trial procedure, intervention, benefits, and potential adverse events of participating in the trial, will be explained to potential participants before they provide informed consent. They will be instructed to provide informed consent after full consideration. The personal information of potential and enrolled participants will be collected and stored by the researchers, who will be required to sign a pledge to protect the confidentiality of the study participants.

### Inclusion criteria

The inclusion criteria are as follows:
Fulfillment of the diagnostic criteria for insomnia according to the Diagnostic and Statistical Manual of Mental Disorders [18];Age 18–65 years (male or female);History of insomnia of at least three times per week for more than 1 month;No history of medication for improving insomnia or the medication must have been stopped for more than 3 weeks;Psychological symptoms including anxiety (self-assessment anxiety scale [SAS] score ≥ 50) or depression (self-reported depression scale [SDS] score ≥ 50);Agreement to participate in the trial and be randomly allocated into any of the study groups.

### Exclusion criteria

Participants who meet any of the following conditions will be excluded:
Presence of insomnia caused by nervous system diseases including stroke, Parkinson’s disease;Presence of serious organic disease, or other chronic diseases, including cardiac disease, liver or kidney disease, or thrombocytopenia with a bleeding tendency;Ongoing pregnancy or being a woman of childbearing age who is not on an appropriate method of birth control;History of severe episodes of fainting during acupuncture or being afraid of blood;Infection or inflammation at the acupoints;Use of alcohol and/or other drugs or dependence on drugs.

### Sample size

Sample size estimation was based on changes in the Pittsburgh Sleep Quality Index (PSQI) score. According to the pre-trial, there was a mean difference in the PSQI of 2.0 with a standard deviation of 4.36 between the two groups. In the current study, we assume a significance level α of 0.05 and power (1-β) = 0.90, owing to which a sample size of 202 can provide effective power to reject the null hypothesis between the manual acupuncture group and sham acupuncture group using two-sided, two-sample *t*-tests assuming equal variance. Considering the expected dropout rate of 20%, this study will require at least 252 participants.

### Randomization and allocation concealment

A simple randomization method will be used in this trial. A total of 252 participants will be randomly assigned to either the manual acupuncture group (*n* = 126, expected) or sham acupuncture group (*n* = 126, expected) after the baseline assessment. The randomization sequence will be generated using Statistical Analysis Software 9.1 by a research assistant who will be blinded to the recruitment of participants. Randomization numbers will be sealed in a computer-generated randomization-based opaque envelope. Only the screening sequence number will be printed on the envelope. The researcher, who screens the eligible patients after baseline assessment, will separate the envelopes, and then assign the patient to the manual acupuncture group or sham acupuncture group.

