#### Data management

For the eligible participants, the researcher will collect baseline data at the appropriate time. The primary and secondary outcomes will be assessed by blinded assessors at baseline and 8 weeks (at the end of the intervention). Data will be collected in the case report form (CRF) by the assessors after obtaining signed consent from the patients. Two research assistants who will be blind to the allocation will double-enter and check the data from the CRF. To protect the privacy of the participants, codes and initials will be used instead of their personal information. All of the original data will be stored in ResMan Research Manager of the Clinical Trial Management Public Platform. The relevant research assistants will be trained to ensure that the system meets the trial requirements. In addition, the research manager will oversee clinical data management by monitoring it at least once a week.

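### The researcher who screens patients also handles the envelopes and assigns the group, and the envelopes carry the screening number, so concealment rests on the seal alone

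*Protocol article*

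**What the plan says.** The procedure is set out in the protocol article under Randomization and allocation concealment.

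- **Who acts at enrolment:** "The researcher, who screens the eligible patients after baseline assessment, will separate the envelopes, and then assign the patient to the manual acupuncture group" or to the sham group. I read separating the envelopes as taking out and opening the one for the patient.
- **What identifies the envelope:** "Only the screening sequence number will be printed on the envelope".
- **Form of the envelope:** "Randomization numbers will be sealed in a computer-generated randomization-based opaque envelope".
- **Who makes the list:** it is generated "by a research assistant who will be blinded to the recruitment of participants".
- **Method:** "A simple randomization method will be used in this trial".
- **Timing:** participants go to the manual group or the "sham acupuncture group (*n* = 126, expected) after the baseline assessment". Under Recruitment, "Before randomization, written informed consent will be obtained from all participants prior to their participation".

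Table 1 puts the eligibility criteria, consent, baseline measurement and randomization in the same column, the week before treatment. It shows no order among them.

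**The concern.** Allocation concealment is meant to ensure that the decision to enrol a person is final before anyone who influences that decision can learn the arm. Two stated features weaken this.

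First, one role judges eligibility, takes out the envelope and assigns the group. Second, the envelope is keyed to the candidate through the screening number, rather than being the next in a randomization sequence. The person judging eligibility can thus tell which envelope belongs to the candidate, and no second person is described at that step.

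The label also weakens the audit trail. With consecutive randomization numbers, a gap in the order of use is a visible breach. With screening numbers, every genuine screen failure leaves an unused envelope, so a candidate turned away after an envelope had been inspected would look the same as any other failure.

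What is at stake is selection at entry. If candidates were taken or refused in the light of the arm, the groups would differ in ways the comparison of PSQI, SAS, SDS and SF-36 cannot separate from treatment. Analysis cannot reliably repair that.

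**Working it through.** No formula applies, so the check is to set the stated steps side by side and ask what each one protects.

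1. **Generation of the list.** A separate research assistant, kept away from recruitment, produces it. This protects the list, but not the envelope once it is in use.
2. **Predictability.** Randomization is simple and 1:1. Earlier assignments therefore say nothing about the next one: the chance of guessing the next arm from the history stays at 1/2. The description of 126 per group as expected fits this. It stops inference from past allocations, but not early opening.
3. **Sealing and opacity.** These stop casual reading of the arm. They are the only stated barrier between the screening researcher and the allocation at the point of use.
4. **Order of steps.** Consent precedes randomization, and assignment follows baseline assessment. SAS and SDS are baseline measurements, so on the stated order the entry threshold of 50 on either scale is scored before assignment.
5. **Eligibility relative to the envelope.** The same sentence places the researcher's screening after the baseline assessment and gives that researcher the envelope next. Some exclusion criteria leave room for judgement, such as serious organic or other chronic disease and fear of blood. The eligibility call and the envelope thus meet in one role at one stage.
6. **Label.** Suppose numbers are given to everyone screened. Then the number is known before the eligibility call, and the number of envelopes used is smaller than the number of screening numbers by the count of screen failures. Unused envelopes are expected and raise no question.

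Taken together, steps 1, 2 and 4 prevent prediction and set a sensible intended order. Only step 3 prevents the arm being seen early, and steps 5 and 6 mean that a breach of step 3 would be easy to make and hard to detect.

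The Discussion shows that the authors see a risk at this stage. Its third limitation is that patients who favour alternative therapies may lean towards real acupuncture, with allocation bias during recruitment as a possible result. The arrangement of the envelopes is not linked to that risk.

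**The case against.** The strongest reply is that the article already describes most of what is expected: an independent list, an unpredictable sequence, sealed opaque envelopes, and consent and baseline assessment before assignment. This stands, and it limits the point to a weak safeguard. A journal article may also leave an envelope custodian and an opening log to the full protocol, so their absence alone would be no finding. The point rests on what is stated: who assigns, and what is printed on the envelope.

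The screening sequence number might also be issued only to people already found eligible. The text does not say. If so, the audit-trail part largely falls away, and the combination of roles remains.

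Some stronger readings are tempting but not supported:

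- **That concealment is defeated or the arm is known before enrolment.** A number on the outside of a sealed opaque envelope ties an unknown arm to a candidate. Learning the arm early would need a breach of the described procedure.
- **That the screening researcher keeps the envelopes.** The text says who separates them, not who stores them beforehand.
- **That the person who assigns groups may also collect week-8 outcomes.** Under Data management, "The primary and secondary outcomes will be assessed by blinded assessors at baseline and 8 weeks", and the Blinding section says assessors are blinded to allocation. Someone who has assigned the groups cannot meet that requirement.
- **That the bias can be put in PSQI points.** This would need the share of candidates steered and how far they differ from those they displace. The document gives neither.

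**Conclusion.** The point holds as a weakness in the stated procedure. The screening researcher also takes out the envelope and assigns the group, and the envelope is identified by the screening number. Concealment at enrolment therefore rests only on the sealed opaque envelope and is open to subversion. The document does not show that allocation is revealed in advance or that any subversion has occurred.

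The size of any resulting bias cannot be estimated. The conclusion on matching envelopes to candidates assumes that screening numbers are issued before eligibility is settled, which is their usual meaning but is not spelled out. The change is worth making because selection bias at entry cannot be put right later, the trial is described as recruiting, and the remedy is cheap.

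**What to change.** Revise the section on randomization and allocation concealment to state that:

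- sealed opaque envelopes are numbered consecutively by randomization number and used strictly in that order;
- each envelope is opened only after consent, eligibility and the baseline PSQI, SAS, SDS and SF-36 have been recorded on the case report form;
- the envelopes are kept and opened by an existing staff member who does not screen, treat or assess outcomes.

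The research assistant who generates the sequence and is blinded to recruitment is one candidate. That person should not be one of the two research assistants who double-enter data blind to allocation. The treating acupuncturists are a less suitable choice: Quality control has them trained on the inclusion and exclusion criteria, so the document does not show that they stand outside eligibility decisions.

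The cost is relabelling the envelopes and moving one task between existing staff. The sample size of 252 and the planned tests do not change. As recruitment is under way, the change protects later enrolments only.

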### Blinding

The outcome assessors, data managers, and statistical analysts will be blinded to the treatment allocation. The manual acupuncture and sham acupuncture assignments will be blinded to the patients. The manipulation of needles and acupoints will be similar in both groups. To assess blinding, the participants will be asked whether they experienced manual acupuncture or sham acupuncture after the trial. It will be impossible to blind the acupuncturists because of the characteristics of acupuncture interventions. Unblinding will only be performed in cases of an emergency, such as any serious adverse event.

### Interventions

All participants will receive 24 sessions of acupuncture (30 min each session, three sessions per week for 8 weeks). Licensed acupuncturists, who have had more than 5 years of clinical experience in acupuncture therapy, will perform the acupuncture treatment. They are well-trained in identifying the locations of the acupoints and the manipulation of needles. The temperature will not be lower than 25 °C in the treatment room. Patients will be allowed to take 0.5–2 mg of Estazolam tablets (Approval number: H37023047, Shandong Xinyi Pharmaceutical Co., Ltd) orally before sleep as a rescue medication. The same acupoints will be used in both groups, including Shenting (GV24), Neiguan (PC6), Shenmen (HT7), Hegu (LI4), Anmian (EX-HN22), Zusanli (ST36), Sanyinjiao (SP6), Zhaohai (KI6), and Shenmai (BL62).

### Manual acupuncture treatment

The patients will lie on their backs in a relaxed position. After disinfection of the skin with 75% alcohol, sterile adhesive pads will be placed on the acupoints. Acupuncture needles 0.30 mm in diameter and 40 mm in length (Suzhou Hwato Medical Instruments Co. Ltd, China) will be used for manual acupuncture. The needles will be inserted through the pads for Deqi sensations, including pain, numbness, swelling, and heaviness sensation, indicating that the acupuncture is effective. The needles will then be maintained for 30 min. Manual stimulation will be conducted three times every 10 min. After 30 min, the needles will be removed, and pressure will be applied with clean cotton balls to avoid bleeding.

### Sham acupuncture treatment

The sham acupuncture group will receive non-insertive acupuncture using blunt-tipped placebo needles (0.30 mm in diameter and 40 mm in length, produced by Suzhou Hwato Medical Instruments Co. Ltd, China). The needles have a blunt tip that cannot penetrate the skin. The acupuncturist will choose acupoints, and the needle placement duration will be the same as for the manual acupuncture group. Sham manual stimulation will be conducted every 10 min. At the end of the treatment, the needles will be removed, and clean cotton balls will be pressed onto the acupoints, so that the patients feel a sensation similar to that of the withdrawal of real acupuncture needles.

### Discontinuation

The participants will be free to stop treatment and withdraw from this trial if they are unable or unwilling to complete the treatment, if the scientific research assistant suggests that it would be inappropriate for the patient to continue the study intervention due to a worsening state, or if adverse events, including subcutaneous hematoma, unfavorable or unintended, and fainting, occur during acupuncture treatment. In addition, patients will be advised to contact their doctors in the event of any undesirable effect after the application of acupuncture treatment. The doctor will diagnose and treat the adverse reactions and provide suggestions on whether to continue acupuncture treatment. The participants who are withdraw from the trial will still be followed up and complete the assessments of primary and secondary outcomes.

### Outcomes

#### Primary outcomes

The PSQI, a self-assessment questionnaire used to evaluate sleep quality, will be the primary outcome of this study. It will be administered at baseline and 8 weeks (at the end of the intervention). The PSQI assesses sleep based on seven domains: subjective sleep quality, sleep latency, sleep duration, sleep efficiency, sleep disturbance, hypnotic medication use, and daytime dysfunction. Each domain is rated from 0 to 3, so the total score of the PSQI ranges from 0 to 21. A cutoff score of 5 indicates insomnia [19].

#### Secondary outcomes

Secondary outcome measures refer to scores on the SAS, SDS, and Medical Outcomes Study 36-Item Short-Form Health Survey (SF-36), which will be assessed at baseline and 8 weeks (at the end of the intervention).

Psychological symptoms, including depression and anxiety, will be assessed using the SAS and SDS. The SAS is applicable to adults with anxiety symptoms and has a wide range of applications. The SDS can fairly directly reflect the subjective feelings of patients with depression and their changes in treatment. A higher total score indicates more severe anxiety and depression [20].

Quality of life will also be assessed as a secondary outcome, using the SF-36, which includes 36 items comprising eight categories: functional capacity (ten items), physical aspects (four items), pain (two items), general health status (five items), vitality (four items), social aspects (two items), mental health (five items), and a question comparing current health conditions with those from a year ago. The total scores range from 0 to 100. Higher scores indicate better health status [21].

Blinding success rate. All patients will undergo the blinding test twice, once each at 4 weeks and 8 weeks, to assess the success rate of participant blinding. The question “When you volunteered for the current trial, you were informed that you have an equal chance of receiving either manual acupuncture or sham acupuncture. Which one do you think you received?” will be asked to them. Patients will have the choice of answering with one of the following responses: manual acupuncture treatment, sham acupuncture treatment, or uncertain.

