#### Safety monitoring

Any adverse event, including subcutaneous hematoma, unfavorable or unintended, and fainting, related to acupuncture treatment will be reported by patients and researchers during each acupuncture treatment. In addition, all participants will undergo liver and kidney function examinations, routine blood tests, and stool tests to exclude severe heart/liver/kidney diseases and evaluate the possible side effects of the acupuncture.

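### Table 1 omits the week-4 blinding test that the outcomes text requires and shows no adverse-event collection in weeks 1–8; the safety text also limits reporting to treatment-related events

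*Protocol article*

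**What the plan says.** On the blinding test, the Secondary outcomes section is specific: "All patients will undergo the blinding test twice, once each at 4 weeks and 8 weeks". It gives the question and three possible answers, one of them uncertain. The Blinding section is briefer and says that "the participants will be asked whether they experienced manual acupuncture or sham acupuncture after the trial". Table 1 has a row labelled "Blinding success rate" with a single tick, in the end-of-intervention column. The column for weeks 1–8, where week 4 falls, is empty.

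On safety, the Safety monitoring section says that adverse events "related to acupuncture treatment will be reported by patients and researchers during each acupuncture treatment". The Interventions section sets 24 sessions, three a week for 8 weeks. In Table 1 the row "Adverse events" has one tick, again in the end-of-intervention column, with nothing under weeks 1–8. The Quality control section has an independent team examine the collected data weekly, with authority to halt the trial over adverse events.

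**The concern.** The article gives more than one schedule for the same measurements. A schedule table is what site staff usually work from, and this one does not prompt a week-4 blinding question.

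The blinding half matters because the PSQI, SAS and SDS are self-assessed, and the Discussion concedes that no objective tools are used. Blinding the assessors protects little when the participant supplies the score, so participant blinding is the main safeguard. It is also under pressure. Real needling aims for Deqi, which includes pain and numbness, while the sham needle cannot penetrate the skin. A guess taken only after the full course is mixed with perceived benefit. An earlier guess helps in reading the later one, and it cannot be reconstructed once week 4 has passed. Trial status says that recruitment is under way.

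For safety there are two issues. One is timing: the table and the text differ. The other is content: if only treatment-related events are reported, someone must judge relatedness before anything is written down. The Blinding section says that acupuncturists cannot be blinded. If they are among the researchers who report, knowledge of the arm could influence which events are recorded.

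**Working it through.** No power or sample-size calculation bears on this point. The check is a comparison of the places that set the timing, with one session count.

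**Is the table intact?** The rows for PSQI, quality of life, depression and anxiety have ticks in the first and last columns. That agrees with the Outcomes and Data management sections, which put these assessments at baseline and 8 weeks. The columns are therefore aligned, and the empty weeks 1–8 cells are unlikely to come from text extraction. No row has a tick in that column.

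**Blinding test**
- Secondary outcomes: weeks 4 and 8, so 2 occasions.
- Table 1: end of intervention, so 1 occasion.
- Blinding section: after the trial, with no mention of week 4.
- Data management: secondary outcomes at baseline and 8 weeks. The blinding success rate is described under Secondary outcomes, so this also leaves week 4 without a slot.

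Difference: 2 − 1 = 1 planned measurement per participant. Only one place in the article carries the week-4 test.

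**Adverse events**
- Interventions: 3 sessions per week × 8 weeks = 24 sessions, which reproduces the stated 24.
- Safety monitoring: reporting at each session, so up to 24 occasions.
- Table 1: end of intervention, so 1 occasion.
- Quality control: weekly review of collected data. This presupposes that events are captured during treatment, so it fits the text and not a literal reading of the table.

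**Relatedness.** Safety monitoring puts the restriction in the sentence that defines what is reported ("related to acupuncture treatment will be reported by patients and researchers during each acupuncture treatment"). It names patients and researchers as the reporters and does not say who judges relatedness.

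**The case against.** The strongest reply is that the text already settles the adverse-event question. Safety monitoring is explicit about every session. The Discontinuation section deals with events arising during treatment and has patients contact their doctors about undesirable effects. Quality control adds weekly review and trains staff in completing the CRF. Against these, one tick in a condensed three-column table may simply mark an end-of-trial summary. This largely stands. It makes loss of session-level events unlikely and leaves the table needing a tick.

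A reader might infer that session-level safety data would be lost at all 252 × 24 = 6,048 sessions and replaced by one recall question each. The documents do not support that. No recall question is described, the CRF is not shown, and the product assumes full attendance despite the expected 20% dropout. It counts sessions, not lost events. Nor can one infer a single end-of-trial question filtered by relatedness: that joins the table's timing to the wording of the section that requires per-session reporting.

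On blinding, the Blinding section does not say that the question is asked only after the trial; it omits week 4 without excluding it. A week-8 or end-of-trial guess survives on every reading. The week-4 guess is not free of perceived benefit either, since 3 × 4 = 12 of the 24 sessions have been given by then. These points limit the harm but do not remove the mismatch between Table 1 and the Secondary outcomes section.

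On relatedness, it is not stated that acupuncturists make the judgement, and all participants also have laboratory tests to look for side effects. Both points are fair. The restriction to related events is nevertheless in the text.

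**Conclusion.** The inconsistency is real and should be corrected. The blinding half is firm: two occasions in the Secondary outcomes section against one in Table 1, with the Blinding section silent on week 4. If staff follow the table, one of the two planned guesses may be missed and cannot be recovered. That outcome is possible, not certain, and depends on whether the CRF and site instructions follow the table or the text.

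The adverse-event timing half is weaker, because the tick can be read as a summary and other sections require ongoing capture. The limit to related events is a separate weakness that rests on the wording itself. A reader might infer that it biases the comparison of safety between arms. The documents show no direction for such a bias and do not settle who judges relatedness, so the supportable statement is that a judgement precedes recording in a trial with unblinded acupuncturists.

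The sample size, power, significance level and primary analysis are unaffected.

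**What to change.** - In Table 1, add the week-4 blinding test to the intervention-period column and keep the end-of-intervention tick. Amend the Blinding section to name both time points, in agreement with Secondary outcomes.
- In Table 1, tick adverse events across weeks 1–8 as well as at the end.
- In Safety monitoring, have all adverse events recorded in both arms, with relatedness to acupuncture as a separate field.
- Bring the CRF into line with these changes.

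The cost is a revised table, small edits to two sections and a CRF check. Participants already attend three times a week, so no visits are added. The downside is that more minor events will have to be recorded. As recruitment is under way, the week-4 item is the most urgent, since guesses missed before the correction stay missing.
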